**Methods:**

This study is a randomized controlled trial using a wait-list control design. One hundred and forty caregiver-patient dyads, recruited from a nationwide database and through the website of the Dutch ALS Center, will be either randomized to a support program or a wait-list control group. The blended intervention is based on Acceptance and Commitment Therapy and consists of 1 face-to-face contact, 6 online guided modules and 1 telephone contact. The intervention can be worked through in 8 weeks. The effectiveness and the participants’ satisfaction with the intervention will be evaluated using a mixed method design. Caregivers and patients will be asked to fill in questionnaires on 4 occasions during the study: baseline, 3 months, 6 months and 9 months. The main study outcome is the psychological distress of the caregiver assessed with the Hospital Anxiety and Depression Scale. Secondary outcomes are caregiver burden, caregiver quality of life, quality of life of the patient and psychological distress of the patient. Group differences in primary and secondary outcomes at 6 months will be compared with linear mixed model analysis. In a subgroup of caregivers we will explore experiences with the support program through semi-structured interviews. Usage of the online modules will be logged.

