### Design

This study is a randomized controlled trial in which caregiver-patient dyads will be randomly allocated to one of two groups:Intervention group (support program during 8–12 weeks).Wait-list control group, receiving care as usual (6-month monitoring preceding the support program).

This design enables us to investigate whether offering a support program in addition to usual care improves the wellbeing of caregivers compared to care as usual. Both caregiver and patient will be asked to complete online questionnaires at baseline (T0), 3 months after baseline (T1), 6 months after baseline (T2) and 9 months after baseline (T3), but only the caregivers will receive the support program. In Fig. 1, the flowchart of the study is presented. In a subgroup of caregivers, we will explore experiences with the support program through interviews.

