#### Online modules

The online part consists of 6 online modules, each module is directed at a specific theme. All modules start with an introduction directed at the theme of the module, followed by psychological exercises. The content of the online modules is focused on the following key components: 1] acceptance (embracing the private events without unnecessary attempts to change them [39]), 2] values (identifying valued domains of life [40]), 3] committed action (actions to pursue one’s values [40]), 4] mindfulness (training conscious awareness and attention from one moment to the next moment [41]), 5] communication about what really matters, 6] cognitive defusion (change the way one interacts with or relates to thoughts by altering the contexts in which they occur [39]). Participants also receive practical information, tips and references to relevant websites, organizations and other sources of information and support associated with the theme of the module. They are able to get in contact with other participating caregivers of patients with ALS or PMA, using the online program. They have an online personal profile and can send each other private messages. Participants can also share tips and advice with fellow participants.

The same psychologist who visited the participant for the face-to-face session provides online feedback including feedback on the completed exercises, a reflection on the progress of the participant and a reaction to any questions or difficulties.

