#### Monitoring adherence to the intervention modules

In order to assess the use of and the adherence to the online modules we will collect log data of the participants such as the frequency of logging in, the duration of logging in, which parts of the modules are downloaded and which functions are used.

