### Analyses

#### Statistical analyses

Descriptive statistics will be used to report demographic variables, clinical outcomes, and the use of the different modules. Group differences in primary and secondary outcomes will be compared with linear mixed model analyses, in which the mediator and covariates will be included. Statistical analyses will be performed primarily according to intention-to-treat and secondarily according to per-protocol principles. The intention to treat analyses will include data of all included caregivers, regardless of their adherence to the intervention or their missing data. In the per-protocol analyses we will only include caregivers who completed at least 4 modules (66.7%) and the T2 measurement. All hypotheses will be tested 2-sided, with a critical value of 0.05. Effect sizes on the primary outcome variable (HADS total) will be calculated with Cohen’s D using the means and pooled standard deviations of the two groups.

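### The secondary per-protocol rule cannot be met by wait-list controls at T2, and applied to the intervention arm alone it breaks the randomised comparison

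*Protocol article*

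**What the plan says.** In the protocol article, Statistical analyses makes intention-to-treat the primary approach and per-protocol the secondary one. It defines the second set in one sentence: "In the per-protocol analyses we will only include caregivers who completed at least 4 modules (66.7%) and the T2 measurement". No arm is named, and no other section gives a separate definition for controls.

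The Design section describes the arms as "Intervention group (support program during 8–12 weeks" and "Wait-list control group, receiving care as usual (6-month monitoring preceding the support program", and places the later assessments at "6 months after baseline (T2) and 9 months after baseline (T3), but only the caregivers will receive the support program". The abstract fixes the time of the comparison: "Group differences in primary and secondary outcomes at 6 months will be compared with linear mixed model analysis". In Table 2, controls evaluate the program only at T3, the nine-month assessment.

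Two further statements bear on the remedy. On adherence, the article says "In order to assess the use of and the adherence to the online modules we will collect log data". The Assessments section says that participants who stop the intervention are still asked for follow-up data.

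**The concern.** A per-protocol set needs a definition of following the protocol that each arm can meet. Here the only adherence criterion is module completion, and one arm has no modules until the outcome of interest has been measured. The rule therefore has to be reinterpreted before it can be run, and the choice of interpretation decides who is compared with whom.

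The natural interpretation, modules for the intervention arm only, brings in a second problem. Completing four modules is something caregivers do after randomisation, and it may go with their level of distress whether or not the program works. Controls are not filtered in the same way. A difference between the two sets then mixes any program effect with the difference between caregivers who complete and those who do not. This is the only planned analysis of the effect in those who used the program, so readers may take it as the answer for users.

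**Working it through.** **1. The plan's own figure.** The threshold is 4 modules, and Online modules states "The online part consists of 6 online modules, each module is directed at a specific theme". 4/6 = 0.667, so the stated 66.7% reproduces.

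**2. Timing.** Controls are monitored for 6 months before the program; T2 is at 6 months; the comparison is at 6 months. By design, a control has 0 modules available before T2, against 4 required.

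**3. Possible readings.**
- Both conditions in both arms, judged at T2: no controls qualify and there is no comparison.
- Both conditions in both arms, counting modules that controls complete after T2: controls are selected on behaviour that follows the outcome, including staying in the study. Nothing in the text suggests this is meant.
- Module condition in the intervention arm only, T2 measurement in both: computable. Controls are then selected on having a T2 measurement but not on adherence.

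**4. Size under the third reading (illustration; m and g are assumed).** Suppose the program has no effect. Let m be the share of the intervention arm below 4 modules, and g the amount by which their T2 HADS would exceed that of completers anyway. With completer mean c:
- intervention arm mean = (1 − m)·c + m·(c + g) = c + m·g
- control mean = c + m·g, by randomisation
- controls minus completers = m·g, a benefit that is not real

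Take g from half the planned difference (3.65/2 = 1.825) up to the full 3.65 points given under Sample size:

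| m | g = 1.825 | g = 3.65 |
|---|---|---|
| 20% | 0.37 | 0.73 |
| 30% | 0.55 | 1.10 |
| 40% | 0.73 | 1.46 |

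The range is about 0.4 to 1.5 HADS points, or 10% to 40% of 3.65. If g is negative, because less distressed caregivers stop, the bias has the same size and works against the program.

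**5. Cross-check with a different model (also assumed).** Let completion depend on a latent normal variable correlated ρ with low T2 HADS, with SD 7.3 from Sample size and completion share p. The spurious difference is ρ × 7.3 × φ(k)/p, with k = z(1 − p). At p = 70% and ρ = 0.3: k = −0.524, φ(k) = 0.348, giving 0.3 × 7.3 × 0.348/0.7 = 1.09 points.

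For the false-positive rate, take 140/2 × 0.8 = 56 caregivers per arm with T2 data, so 56 × 0.7 = 39.2 completers against 56 controls. SE = 7.3 × √(1/39.2 + 1/56) = 1.52, and the nominal 5% two-sided error becomes about 11%. Over p = 50–90% and ρ = 0.1–0.5, the spurious difference runs from 0.14 to 2.91 points and the error from about 5.1% to 41%.

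**6. Primary analysis.** The intention-to-treat set takes all included caregivers regardless of adherence or missing data. Nothing above enters it.

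**7. Price of a complier-average estimate.** With no control access before T2, the estimate is the intention-to-treat difference divided by p, and its SE grows by about 1/p: 1.25 times at 80% compliance, 1.43 at 70%, 1.67 at 60%.

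**The case against.** The strongest reply is that a control follows the protocol by receiving usual care for six months, so the module criterion plainly belongs to the arm that is offered modules. On that reading the analysis can be run, and what is missing is one clarifying clause. Selection on adherence is a familiar limit of any per-protocol analysis, which is why this one ranks below intention-to-treat.

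Much of this stands. A reader might infer from the literal wording that the analysis is impossible; the empty-arm reading makes no sense of the design and is unlikely to be intended. A reader might also infer that the bias must favour the program. The article does describe caregivers as short of personal time, which makes heavier-burdened dropouts conceivable. But it gives no completion rate and no link between adherence and HADS, and caregivers with little distress may equally see little reason to continue. The covariates in the planned mixed models could also absorb part of any difference.

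What does not stand is that this is detail an article may leave to a later document. The article fixes the set with an exact threshold, and as fixed it fails for one arm. The charitable reading repairs the computation but not the comparison.

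**Conclusion.** The point holds for the secondary per-protocol analysis. The timing argument rests only on the documents: zero modules are available to controls before T2, against four required. Under the intervention-arm-only reading, the result is a non-randomised comparison of adherers with controls not selected on adherence.

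The magnitudes, 0.4–1.5 points in the simple illustration and 0.14–2.91 in the wider one, depend on assumed completion shares and assumed links with distress, and they ignore covariate adjustment. They show that the bias could be material against a 3.65-point target. They do not predict its size or sign.

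It would be wrong to conclude that the trial's main result is at risk. Intention-to-treat is primary and untouched. This is something that should be fixed, not a defect that must be cured before the trial can answer its main question.

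**What to change.** Amend the analysis wording in three ways.

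1. **Define the per-protocol set by arm.** The module criterion applies to the intervention arm only; controls qualify by having had no program access before T2. Label the analysis descriptive.
2. **Estimate the effect in program users** as a complier-average causal effect on HADS at T2: randomisation as instrument, compliance as at least 4 modules from the log data, baseline HADS and the stratification factors as covariates, and missing T2 outcomes handled consistently with the intention-to-treat analysis. Controls have no access before T2, so non-compliance is one-sided by design.
3. **Add a sensitivity analysis** with compliance defined as any program contact, including the face-to-face session.

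The cost is wording. Module logs are already planned, and those who discontinue are still asked for follow-up; contact at the face-to-face session must also be recorded.

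There are two statistical downsides. The interval widens as in step 7. The four-module estimate also assumes no effect below the threshold, although such caregivers may have had the session with the psychologist and up to three modules. If partial users, a share q of the arm, gain τ, the estimate exceeds the true complier effect by (q/p)·τ. The any-contact analysis tests that assumption only in part.

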#### Interview analyses

Interviews will be transcribed and analyzed thematically [64]. The texts will be broken down into fragments based on content and fragments will be labeled with a code using NVIVO 10 [65, 66]. Once the coding of all interviews has been completed, codes will be sorted according to similarities and overarching themes and subthemes will be identified.

## Discussion

To our knowledge, this will be the first study to evaluate a blended support program for caregivers of ALS and PMA patients. The program is aimed at enhancing feelings of control over caregiving tasks using ACT principles. Previous research on ALS caregiving revealed increasing levels of psychological distress in caregivers, a lack of existing interventions and an urgent need for support [7, 21]. ACT interventions have proven to reduce psychological distress in other caregiver populations [27, 28] and are valuable in contexts with circumstances that cannot be changed [23, 24].

A strength of this intervention is the blended approach: face-to-face support in combination with online support. Due to the many hours ALS and PMA caregivers spend on providing care, they often experience a lack of personal time [17], which reduces the opportunity to access traditional forms of support. Therefore, the blended approach may provide support in a more time-efficient manner, as caregivers can access information and exercises any time at home via an online platform.

Although previous research has provided information on factors associated with psychological distress and burden [e.g. 15], the underlying process is still unclear due to a gap in research on personal factors related to the caregiver. The use of a theoretical framework is considered as another strength since it helps to gain insight into whether the demand-control theory is applicable to the caregiver situation in ALS and PMA [18] and will provide knowledge on the influence of factors such as control and mastery in relation to psychological distress and burden. This will provide information to understand how, when and for whom the intervention will be effective.

Further, caregivers and healthcare professionals were involved in both the development process of the intervention and the design of the study. Due to their involvement, we were able to develop an intervention that meets the needs and wishes of caregivers and includes the most important themes according to professionals. Caregivers and professionals will also be involved in the next steps of the research such as the recruitment and the dissemination of the results of the study. Previous studies indicated that engaging the target group increases study enrollment and may enhance the uptake and the acceptance of interventions [67, 68].

Another strength of the study design is the mixed method approach; questionnaires and interviews will be used to evaluate the program which enables a throughout evaluation and may lead to further improvement of the support program.

The support program may also have some weaknesses. First of all, the online part of the support program might be an obstacle for some caregivers due to a lack of information and communication technology literacy. These caregivers might prefer to receive traditional face-to-face support.

Another limitation might be that the intervention is only focused on partners, which means that primary caregivers who have another type of relationship with the patient are excluded while they might be in need of support. Once the intervention has proven to be effective, it might be worthwhile developing an adapted version for primary caregivers with other relationships to the patient.

A limitation of the study design might also be contamination with care as usual. In the last couple of years, the value and the importance of the social environment of patients has been emphasized. This has led to a stronger focus on caregivers in standard care; care facilities are encouraged to involve caregivers in their care plans. Due to this recent shift, the support for caregivers might have improved and it may be more difficult to demonstrate a significant difference when we compare care as usual with our support program. However, if caregivers perceive the support program as being more user-friendly than care as usual, this will encourage its use in standard care.

To conclude, this study will provide insight into the effects of a blended support program for informal caregivers of patients with ALS and PMA by targeting feelings of control over caregiving tasks using ACT principles. The program could potentially benefit caregivers, and might affect patients’ wellbeing indirectly.

### Dissemination plan

Results of this study will be published in international, peer-reviewed journals and presented at relevant conferences/congresses, both national as well as international. Results will furthermore be communicated through national publications and published on relevant websites.

## Abbreviations

ACT: Acceptance and Commitment Therapy
ALS: Amyotrophic Lateral Sclerosis
ALS-FRS-R: Amyotrophic Lateral Sclerosis Functional Rating Scale-Revised
ALS-FTD-Q: Amyotrophic Lateral Sclerosis-Frontotemporal Dementia-Questionnaire
CarerQoL: Care Related- Quality of Life
CSQ-8: 8-item Client Satisfaction Questionnaire
HADS: Hospital Anxiety and Depression Scale
iVICQ: institute for Medical Technology Assessment Valuation of Informal Care Questionnaire
MPSS: Multidimensional Scale of Perceived Social Support
MQOL: McGill Quality of Life Questionnaire
PMA: Progressive Muscular Atrophy
SPBS: Self Perceived Burden Scale
SPIRIT: Standard Protocol Items Recommendations for Interventional Trials
SRB: Self-Rated Burden scale
TIDieR: Template for Intervention Description and Replication
ZBI: Zarit Burden Interview
